### Treatment

To understand the features of both PREPARE conditions, first current care in pain rehabilitation in the Netherlands will be explained. Thereafter, both PREPARE conditions are described. At last, the role of the nurses is illustrated.

#### Current care in pain rehabilitation

In the current pain rehabilitation treatment in the Netherlands [41] roughly four phases can be identified. The specific content of the phase can differ per center.

The four phases are:

1. Screening: In this phase, a patient’s eligibility and readiness for pain rehabilitation is assessed. Also information is provided by either a consultant in rehabilitation medicine or a nurse practitioner. In most centers for this purpose use existing educational material, such as ‘De pijn de baas’ (‘Mastering pain’) [42] or ‘Explain Pain’ [43] (WPN, 2012, internal document) are used as information tools for this purpose. In most places, information is given before the definite start of the treatment.

2. Observation: A patient’s pre-treatment situation and motivation is assessed, and the most suitable type of treatment is selected. In some centers, this phase takes two or three sessions in 2 to 4 weeks. Often this is accompanied by the use of self-report questionnaires.

3. Rehabilitation treatment: The multidisciplinary pain rehabilitation treatment lasts for around 3 months with an intensity of 2 or 3 days a week on average. Depending on the patients’ limitations and underlying problems, different treatment approaches such as graded activity and/or graded exposure are used in combination with other psychosocial and physical interventions.

4. Aftercare and post rehabilitation treatment assessment: Booster sessions, tailored to patients’ needs, are given for relapse prevention and long-term facilitation of applying learned skills to maintain and further improve participation. The moment of the assessment is around 6, 12, 24, to 52 weeks post-treatment. These follow-up appointments are mostly accompanied by completion of self-report questionnaires for treatment evaluation. It has to be said that this is not routine care in all Dutch rehabilitation centers.

#### PREPARE conditions

The PREPARE intervention focuses on phase one. This is also the period during which patients are waiting before they can start their actual treatment (observation and rehabilitation treatment). During the study, patients will receive either the new MI-based intervention or care as usual. In order to standardize treatment options, both arms (MIP as well as UC) will include two sessions with identical contact time. In order to prevent contamination of treatment, each treatment condition will be delivered by different nurses. Figure 1 illustrates the situation during the PREPARE study.

1. Usual care (UC)

**Figure 1 F1:**
[figure not shown]
Flow-chart of the design of the PREPARE study (apart file).

In the usual care (UC) arm, participants will receive pain education according to the information ‘De pijn de baas’ [40] (Mastering pain). The ultimate goal is to provide the participant with information about, for example, differences between acute and chronic pain, its nature, and strategies to handle cognitions about pain.

2. MIP intervention condition

The MI intervention condition is based on the four general principles of MI, which are incorporated into all sessions in the MIP condition [44]:

1. Expressing empathy by the use of reflective listening,

2. Developing discrepancy between client goals and current problem behavior,

3. Rolling with resistance by avoiding argumentation by assuming that the client is responsible for the decision to change,

4. Supporting self-efficacy and optimism for change [44].

The features of both MIP and UC are mentioned in Table 1.

**Table 1 T1:** Features of the two interventions

**Motivational interviewing based pre-treatment (MIP)**	**Pain education (Usual care (UC))**	
Goal: explore participant’s life situation, impairments and ambivalences in order to enhance intrinsic motivation	Goal: provide the participant with information	Goal
General principles of MI	General principles of health education and patient education	Basic principle
Content based on patient-driven topics derived from the ICF-model	Content based on the book ‘De pijn de baas’ [42] (Mastering pain)	Foundation
Content sessions tailored to the patients’ readiness to change	Content is fixed by means of the treatment protocol	Protocol rigidity
Exploration actual (life) situation, burden and impairments of the chronic pain in daily life	Provision of general health education about topics related to chronic pain	**Content first session**
Assessing + enhancing motivation, self-efficacy, and readiness to change for behavior	Provision of information regarding core elements of pain rehabilitation	
Giving feedback adapted to the state of readiness-to-change	Continuation of general health education about topics related to chronic pain	**Content second session**
Continuation exploration		
Continuation assessing + enhancing motivation, self-efficacy, and readiness to change for behavior		
Is given related to the stage of change of the participant according to the MI-principles	Is not given	Feedback

The nurse is directive within this process, but the participants’ autonomy is strengthened and his or her right to decide on everything related to the person is respected.

During the first appointment, a trustful relationship between participant and nurse is built, the actual (life) situation, burden, and impairments of the chronic pain in daily life, motivation, self-efficacy, and readiness to change behavior is assessed and enhanced. Next, the session is summarized and closed. The second appointment starts with a brief motivational feedback session. The process of the first appointment will be discussed with the participant by giving feedback adapted to the state of readiness-to-change. Therein, motivation and self-efficacy for behavior change is enhanced. In addition, topics related to chronic pain and treatment, such as education about the influence of exercise and a background in the bio psychosocial approach will be discussed. Next, the session is summarized and closed.

#### Nurses

Both UC and MIP are administered by registered nurses working in the field of rehabilitation. In order to prevent contamination of treatment by components of the other intervention, nurses will be trained and only guide participants in one specific condition. The two nurses selected to deliver the MI condition, are both experienced MI coaches (4 years of experience). To assure optimal quality of the MI condition, both nurses receive an expert training by a certified MI trainer: their MI knowledge and experience in the context of chronic pain rehabilitation are updated based on an evidence-based training tailored to their specific needs [45-49]. During the study the MI sessions will also be audio taped and the MI quality will be assessed using a coding instrument (Motivational Interviewing Treatment Integrity (MITI)) (see also Methods section, Process evaluation section). Subsequent training will be based on additionally regular supervision, done by training on the job and direct feedback on MIP sessions.

Quality of the UC condition:

The two nurses selected to deliver the usual care condition are experienced in the field of rehabilitation (20 years and 5 years, respectively).

Before the start of the study, they will receive a 3-h refresher training in general communication skills and general principles of health education. In addition, the content of relevant chapters of the book ‘Mastering pain’ is discussed. During the study, the nurses of the UC condition will meet once or twice a year to discuss problems encountered during the sessions.

### Data collection

For the (cost-) effectiveness evaluation, measurements will be carried out before the first MIP/UC pre-treatment sessions (T0), after the MIP/UC (T1 = post pre-treatment), after the regular multidisciplinary pre-rehabilitation assessment (before starting rehabilitation), at the start of the pain rehabilitation treatment (T2), after treatment completion (T3), and at 6-month follow-up (T4). Study assessments at T0, T2, and T3 will be integrated in current care clinical assessment battery pre-rehabilitation and post rehabilitation (see also Figure 1 (flow-chart) and Table 2). Cost measurements will be carried out at three points: T0, T2, and T4. Information on drop-out from and adherence to the (pre-) rehabilitation treatment, start and end date of the treatment, and no show are derived from the administrative patient registry.

**Table 2 T2:** Outcome measures, abbreviation instrument, and assessment moments PREPARE study

		**Baseline**	**Two sessions**	**After pre-treatment**	**Start pain rehab treatment**	**Finish pain rehab treatment**	**6 months after T3**
	**Abbr.**	**T0**^**a**^		**T1**	**T2**^**a**^	**T3**^**a**^	**T4**
**Covariates**							
Demographics patient		x					
***Primary outcome effect evaluation***							
Participation	USER-P	x		x		x	x
***Secondary outcomes effect evaluation***							
Physical functioning/disability	PDI	x			x	x	x
Pain intensity	VAS	x			x	x	x
Main complaints	PSC	x			x	x	x
Drop-out/adherence				#		#	
Self-efficacy/perceived competence	GSE	x		x		x	x
Pain-specific self-efficacy scale	CPSS_V2	x		x		x	x
***Cost-effectiveness evaluation***							
Cost questionnaire	Tic-P	x			x		x
Productivity losses	SF-HLQ	x			x		x
Quality of life/health status	SF-36	x			x	x	x
**Potential active ingredients MI**							
Stages of change	MPRCQ 2	x		x			
MI integrity/fidelity			*				
**Potential moderators**							
Credibility and expectancy of the treatment	CEQ	x		x	x		
Motivation	TMQ	x		x			
Depression	BDI	x			x	x	
Acceptance	AAQ-II	x		x		x	
Flexible goal-adjustment	FGA	x		x		x	
**Process evaluation**							
Satisfaction with (pre-)treatment				x +			
Client-centeredness	CCCQ			x			
Feasibility				+			

x Questionnaires in patients.

+ Questionnaire in nurses.

# Process measures.

* Audiotapes.

^a^Alongside usual care assessment.

As patients have to incorporate learned behavior into daily routine functioning, the improvement of participation, the ultimate goal of pain rehabilitation, is not optimal directly after treatment. We expect relevant change in the level of participation to occur at 6 months. Therefore this time point is chosen as our last measurement moment. Due to the fact that the PREPARE trial is embedded in clinical practice, the measurement moments are not precisely planned at the same moment. Especially the waiting list period between T1 and T2 may vary and furthermore the total duration of the pain rehabilitation treatment may vary between 10 to 16 weeks.

### Demographic and medical variables

Baseline assessment includes: gender, nationality, marital status, educational level, and co-morbidity, as well as pain location and pain duration.

In addition, baseline assessment includes the following risk factors for attrition: sick leave [50], level of being active in sports, smoking status [18], level of physical functioning [50], pain intensity [50,51], perceived disability [51], low treatment satisfaction [52], and expectations regarding the content of the treatment [53].

### Outcome measures

Outcome measures (parameters) and assessment moments are presented in Table 2.

#### Primary outcome

The primary outcome of the effect-evaluation will be the mean difference in change in level of participation of the participants at T4 compared to T0 (baseline).

Participation will be measured by the Utrecht Scale for Evaluation of Rehabilitation-Participation (USER-P) [54]. It consists of 32 items and covers three aspects of participation, namely Frequency, Restriction, and Satisfaction. The subscale Frequency consists of 12 items and assesses vocational activities, and frequency of leisure activities and social activities. Each item is scores from 0 (‘not at all’) up to 5 (‘36 hours or more’/’19 times or more’). The subscale Restriction comprises 10 items assessing experiences in vocational and leisure activities. Items are rated on a four-point Likert scale ranging from 0 (‘not possible at all’) to 3 (‘independent without disability’). The subscale Satisfaction consists of 10 items and rates satisfaction regarding participation in daily life issues such as work and social relations. Items are rated on a five-point Likert scale ranging from 0 (‘not satisfied at all’) to 4 (‘very satisfied’). Higher scores reflect more social participation (each higher frequency, less restrictions, higher satisfaction). The psychometric qualities validity and reproducibility are satisfactory [36,55].

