### Hypotheses

1a. It is expected that patients’ level of social participation will be higher in the MIP intervention condition compared to the UC after pain rehabilitation treatment and at 6-month follow-up after finishing the rehabilitation treatment.

1b. It is hypothesized that drop-out rates will be lower and adherence to the treatment and the level performing daily activities) will be higher in the MIP condition compared to the UC.

2. It is hypothesized that MIP will be more efficient compared to UC, both in effects as well as utilities.

3. It is hypothesized that the MIP intervention is feasible for the participating nurses and the MI fidelity of the MIP intervention is sufficient.

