### Sample size

The sample size calculation is based upon an estimated difference in change in level of participation between baseline and 6-month follow-up (after completion of the rehabilitation treatment) as assessed by the Utrecht Scale for Evaluation of Rehabilitation-Participation (USER-P) [35,36]. Reproducibility [37], responsiveness [38], and validity [37] of the USER-P are satisfactory. As participation is the important outcome in rehabilitation, we have chosen this as primary outcome. The scale consists of the three aspects of participation represented by the subscales Frequency, Restriction, and Satisfaction. The sum score of each subscale is converted to scores on a scale ranging from 0 to 100. There is no USER-P total score.

Our sample-size calculation is based upon the subscale Satisfaction. This subscale is the most important part of participation as it marks the subjective experience of participation [9]; therefore we have chosen this one.

As at this moment no information is available about the USER-P in a pain population regarding normative values, clinically relevant change, and clinically relevant difference, our study is exploratory of character. In a study by van der Zee (2011) the USER-P is taken in different patient groups at three different points in time [38]. As these groups were part of a cohort study, nothing is known about differences after a specific treatment. We know from other studies that multidisciplinary pain rehabilitation treatment is moderately effective with effect sizes ranging from 0.30 for behavioral outcomes up to 0.40 for functional outcomes [14]. We expect an additional effect for the MIP intervention since systematic reviews of motivational interviewing-based interventions show an effect size ranging from 0.27 up to 0.40 when compared with a weak comparison group [30-32,39]. It has to be said that in those reviews no study in the field of chronic pain or rehabilitation treatment was taken into account. Therefore, our power calculation is based on the following two assumptions:

1. Using an expected mean change of 5 points within UC is expected whereas a difference of additional 5 points (thus at least 10 points in total) within MIP in the USER-P sub scale Satisfaction is considered as clinically relevant. Those numbers are estimates as the clinically relevant difference is not known yet.

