#### Effect evaluation

Baseline data will be analyzed to describe the characteristics of all participants and to check for significant imbalances between the two groups. Possible baseline differences between the intervention group and the control group will be tested by an independent samples *t*-test (normal distribution) or Mann–Whitney U tests (non-normal distribution) in the case of continuous variables. In the case of dichotomous variables, a Chi-square test will be used. In case of imbalances in prognostic factors between both randomized groups, an adjustment for those factors will take place. The number of drop-outs and follow-up losses in both groups will be reported based on descriptive data. Differences in primary and secondary outcome measures between MIP and UC will be analyzed using repeated measurements techniques and multilevel analysis. This approach is chosen because repeated measures within individual subjects are taken. A *P* value <0.05 is considered statistically significant. Data will be analyzed according to the intention-to-treat principle. All outcomes will be assessed at each follow-up moment by taking into account a specific a priori hypothesis. Additionally, per protocol analyses will be performed to assess whether protocol deviations have caused bias.

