### Economic evaluation

In the economic evaluation, cost and effects of usual care and MIP will be calculated and compared. Therefore, the cost per patient year (=participant year) will be calculated. This means that all observed costs will be extrapolated to a 1-year period.

The analysis will include those persons for whom at least two of the three follow-up measurements (cost diaries) are available.

For the cost-effectiveness analysis (CEA) the cost-effectiveness ratio will be stated in terms of costs per improvement on participation (as assessed with the USER-P).

For the cost-utility analysis (CUA) the cost-utility ration will be stated based on the cost per (Quality Adjusted Life Year) QALY gained.

Bootstrap (5,000 times) re-sampling techniques will be used to test for differences and uncertainty in costs and effects between the MIP and the UC intervention.

The bootstrapped cost-effectiveness and cost-utility ratios will be subsequently plotted in a cost-effectiveness and cost-utility plane. The results of this study will also be depicted in cost-effectiveness acceptability curves (CEACs) [104].

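### The primary outcome section does not say which of the three USER-P subscales carries the primary test at T4, or which one serves as the cost-effectiveness effect

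*Protocol article*

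**What the plan says.** The Primary outcome section sets the endpoint as "the mean difference in change in level of participation of the participants at T4 compared to T0 (baseline". It then says that the USER-P "covers three aspects of participation, namely Frequency, Restriction, and Satisfaction", and describes the items and scoring of each in turn. It singles none of them out.

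The Sample size section explains that each subscale is rescaled to 0–100 and that "There is no USER-P total score". It continues: "Our sample-size calculation is based upon the subscale Satisfaction". Its reason is: "This subscale is the most important part of participation as it marks the subjective experience of participation". The same section names participation as a whole, not Satisfaction, as the chosen primary outcome, and calls the study exploratory because no USER-P reference values exist for a pain population.

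The abstract, hypothesis 1a and Table 2 refer only to participation. Under Effect evaluation, P<0.05 is the significance threshold for primary and secondary outcomes, and no order among the USER-P subscales is given. The section Cost-effectiveness and cost-utility sets costs against the primary outcome measure, and under Economic evaluation "the cost-effectiveness ratio will be stated in terms of costs per improvement on participation (as assessed with the USER-P"). Neither names a subscale.

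**The concern.** With three scores and no total, change in participation is not one number. Three different T4 contrasts fit the definition equally well, and the article gives no rule for what to conclude if they disagree, for instance if Restriction improves and Satisfaction does not. The 80% power and the 5% error rate were worked out for one contrast only. If the choice of subscale is still open when results are seen, the headline claim can follow whichever subscale reached significance. The cost-effectiveness ratio could also be built on a different subscale from the one behind the clinical claim.

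**Working it through.** **1. What the stated sample size covers.** Inputs from the Sample size section: mean change 10 versus 5 points on Satisfaction (difference 5), SD 10, two-sided α = 0.05, power 80%, 20% drop-out. Equal arms come from the randomization section.

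- Standardized effect: d = (10 − 5)/10 = 0.5.
- Normal approximation: n per arm = 2(1.960 + 0.842)² / 0.5² = 62.8, so 63.
- t-test version: 63.77, so 64 per arm and 128 in total. Power at 64 per arm is 80.1%.
- Drop-out: 128/(1 − 0.20) = 160.

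The stated 128 and 160 are reproduced exactly. They are the size for one test, on one subscale, at 0.05.

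**2. Error rate if any of three subscales at T4 may carry the claim.** With independent tests:

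1 − (1 − 0.05)³ = 1 − 0.857 = 0.143.

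Subscales of one questionnaire answered by the same patients are unlikely to be independent, and the article gives no correlations. The values below are therefore assumptions. Each result comes from 2 million simulated sets of three equally correlated normal test statistics under no effect, counting sets in which at least one exceeds 1.96 in absolute value.

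| Assumed correlation | Chance of at least one P<0.05 |
|---|---|
| 0 | 14.3% |
| 0.3 | 13.6% |
| 0.5 | 12.5% |
| 0.7 | 10.9% |
| 0.9 | 8.4% |

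These figures are two-sided, as is the stated 5%. Every one is above 5%.

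**3. What keeping three co-primary subscales would take.** Assume d = 0.5 on each and a Bonferroni level of 0.05/3 = 0.0167. The t-test then needs 86 per arm, or 172 evaluable, and 172/0.80 = 215 randomized (216 for equal arms). With the planned 64 evaluable per arm, power per subscale would be about 66%.

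**4. The cost-effectiveness ratio.** Each subscale has its own 0–100 score, so three different effect differences, and hence three different ratios, satisfy the text. The cost-utility ratio uses QALYs derived from the SF-36 and does not depend on the choice.

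**The case against.** The strongest reply is that Satisfaction has in effect been chosen. The Sample size section calls it the most important part of participation, sets the clinically relevant difference on it, and rests effect size, power and N on it. This stands as good evidence of intent, and it makes the repair easy. But the selection is worded as the basis of the calculation, and it does not reappear in the outcome, analysis or economic sections.

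A second reply is that the study is described as exploratory. That softens the point without removing it, since the article also declares a primary outcome, a power calculation and a significance threshold.

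A third is that ranking subscales and handling multiplicity can be left to the analysis plan. That is fair for secondary outcomes. Here, though, the article gives the primary outcome its own section and defines it by a quantity that cannot be computed as a single score.

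It is also true that no sentence says success on any one subscale is enough. The error rates above show what the text leaves open, not a rule that it adopts.

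Two stronger readings are tempting and are not supported:

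- **Adding T3.** Hypothesis 1a expects a benefit "after pain rehabilitation treatment and at 6-month follow-up after finishing the rehabilitation treatment", and the analysis section says "All outcomes will be assessed at each follow-up moment", so a reader might count six tests over T3 and T4. But the Primary outcome section fixes T4 against T0, and the Data collection section explains that participation is not expected to be at its best straight after treatment. Hypothesis 1a is a joint expectation about both times, and the analysis sentence goes on to tie testing to a prior hypothesis. Nothing lets T3 carry the primary claim.
- **No denominator at all.** A reader might infer that the cost-effectiveness ratio cannot be formed. It can, on any of the three subscale scores. What is missing is which one.

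**Conclusion.** The concern holds for the choice of subscale at T4. The primary endpoint is open among three scores, while size and power were computed for one of them. If any of the three could support the claim, the false-positive chance would lie between 8.4% (assumed correlation 0.9) and 14.3% (independence), not at 5%. The range rests on assumed equal correlations, because the article reports none. The sample size is correct for its stated purpose, and the primary time point is settled. The cost-effectiveness effect measure shares the same gap, and one decision closes both.

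**What to change.** In the Primary outcome section, name the change in USER-P Satisfaction from T0 to T4, compared between arms at two-sided 0.05, as the single primary endpoint. List Frequency and Restriction as secondary. In Cost-effectiveness and cost-utility and in Economic evaluation, name the same Satisfaction change as the effect measure. This follows the article's own rationale for choosing Satisfaction and is the contrast for which the trial was sized.

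The change is one of wording: N stays at 128 evaluable and 160 randomized, and no new data are needed. The small cost is that a favourable result on Frequency or Restriction could no longer carry the primary claim. Keeping all three as primary is possible, but only with an adjusted level and the larger trial, or lower power, shown above.
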